### 2.2. Secondary outcome

The secondary outcome will include nutrition of trauma patients, associating the loss of muscle mass with caloric and protein intake and laboratory changes caused by the stress of traumatic brain injury, such as levels of creatinine, albumin, total protein fractions, protein c reactive, blood count, platelet count and bilirubin.

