### 3.3. Study procedures

#### 3.3..1.
*Study protocol*.

Anthropometric, clinical and nutritional data will be collected: height, weight, BMI, injury severity score,^[21]^ prognostic scores SAPS-3^[22,23]^ and APACHE II,^[24]^ number of days of mechanical ventilation and ICU and hospital stay,^[3]^ NUTRIC score,^[25]^ NRS 2002^[26]^ and basal energy expenditure through pocket formula with calorie and protein requirements.

Weight will be measured on a Stryker scale stretcher, height will be used standard body tape measure, measurements will be taken at the time of admission of the patient to the ICU. BMI will be classified according to the World Health Organization 1995.^[27]^

Daily, the volume of diet and protein intake will be recorded until the seventh day of hospitalization, and the percentage of diet intake will then be calculated by the ratio of the amount actually ingested to the amount prescribed.

The USG will be performed with a Sono Site M-Turbo device with 2-dimensional mode, with a linear transducer (frequency: 7–13MHz) to get high-resolution images of surface structures 1, in cross-section, in B-mode, with the transducer oriented transversely to the longitudinal axis (the imaginary line marked before) of the thigh forming a 90° angle in relation to the skin surface with minimal pressure on the skin (Fig. 1).

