**Figure 2. F2:**
[figure not shown]
Compendium of study design.

Measurements will be got by 2 operators, intensive care physicians, trained in using bedside USG in the ICU. The standardization of USG measurements was previously published, whose correlation analysis found an excellent interobserver relationship (*R*2 > 0.90)^[28]^

Care will be taken during the handling of patients so that all measurements do not entail greater risks for them, except for the discomfort caused by the exam. The same examiner will make all measurements and, at the same point, as we will mark the studied limb with a marker pen and cover with plastic film.

We will perform the tomographic control exams of the thigh only in the studied region through the marking performed, to reduce: radiation dose to patients, costs and exam time. The CT analyzes will be interpreted by a radiologist and we will have 3 images per patient.

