### 3.4. Statistical analysis

Initially, the Shapiro–Wilk test will be performed to evaluate the data distribution. Mean or median depending on the distribution of variables will describe data. To compare the values of quadriceps femoris thickness, Student’s t test or Wilcoxon test for paired samples will be applied, depending on the distribution of variables. Bland & Altman test will also be performed to assess the agreement between the methods. The relationship between caloric and protein intake, laboratory alterations and loss of muscle mass will be evaluated through multiple linear regression, with muscle mass being considered a dependent variable and caloric and protein offers and laboratory alterations being independent variables. We will use the STATA version 14 program for the analyses.

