Another observational study,^[34]^ aimed to evaluate the role of muscle ultrasound in the analysis of nutritional status in 29 patients admitted to the ICU, identified the greatest loss of muscle mass in the first week of hospitalization, having a direct association with the patient’s nutritional status. Although BMI is a commonly used parameter for screening nutritional status, it does not show the amount of muscle loss in these patients.^[35,36]^ In contrast, USG is a valuable and practical measurement tool that may hold promise in helping to guide metabolic support that allows morphological changes in muscles to be assessed in critically ill patients.^[37]^

It is also important to note how safe and viable the tool is. In patients with severe trauma, the use of quadriceps USG was easy to perform and reliable even in the hands of less experienced operators.^[38]^ Thus, USG ends up gaining ground for its ease of use and lower costs.

Our study can contribute to the use of USG in critically ill patients with muscle loss, not only by recognizing patients with a more fragile nutritional component but also by differentiating the more severe patients who are at greater risk of unfavorable evolution in the ICU. We believe USG is a noninvasive and easy-to-operate tool to distinguish patients on mechanical ventilation who have muscle wasting by analyzing quadriceps thickness, and thus early approaches could be applied to optimize treatment.

The novelty and importance of this project lies in using a method for assessing muscle mass through ultrasound of the quadriceps femoris, a noninvasive, low-cost bedside method that is feasible in critically ill patients.

In this study, we propose, unprecedentedly, performing a validation study of ultrasound with the gold standard (GS) to evaluate the musculature of critically ill patients victims of traumatic brain injury. The results got will be fundamental for the development of new fields of investigation and may contribute to the discovery of a new approach to treat sarcopenia in critically ill patients.

This study has limitations, such as the characterization of the study population in terms of age and sex, trauma severity, fluid balance, and associated comorbidities, which can affect both muscle thickness and outcomes. In addition, this is an observational study in a single center, which certainly has limitations in the patient profile and regional variations.

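### Section 3.4 regresses muscle mass on intake and laboratory values together, without admission thickness or severity, so the intake coefficients do not cleanly answer the question about muscle loss

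*Protocol article*

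**What the plan says.** Section 2.2 of the protocol article gives the secondary outcome as "associating the loss of muscle mass with caloric and protein intake and laboratory changes caused by the stress of traumatic brain injury", and lists the laboratory items by example: "such as levels of creatinine, albumin, total protein fractions, protein c reactive, blood count, platelet count and bilirubin". Section 3.4 states the analysis in one sentence. Its first half gives the aim: "The relationship between caloric and protein intake, laboratory alterations and loss of muscle mass will be evaluated through multiple linear regression". Its second half assigns the roles: "with muscle mass being considered a dependent variable and caloric and protein offers and laboratory alterations being independent variables". No separate intake model is described.

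On intake, section 3.3 says: "Daily, the volume of diet and protein intake will be recorded until the seventh day of hospitalization". The same section collects the injury severity score, SAPS-3 and APACHE II. Thickness is measured at three times, and for CT "we will have 3 images per patient". The Discussion gives as limitations "age and sex, trauma severity, fluid balance, and associated comorbidities, which can affect both muscle thickness and outcomes". None of these factors is named in the section 3.4 model.

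**The concern.** The secondary question is whether patients who receive more calories and protein lose less muscle. Four features of the sentence in section 3.4 stand in the way of a clear answer.

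- The aim is loss, but the dependent variable is muscle mass. Whether that means a level or a change from the first measurement is not said, and admission thickness is not named as a covariate.
- Severity is not named, although the authors say it can affect thickness and outcomes and already collect three scores for it.
- The laboratory values sit beside intake as predictors with no stated role or timing. Section 2.2 attributes them to the stress of the injury. Section 1.1 says that loss of muscle can itself raise inflammatory cytokines, so an inflammatory marker such as C-reactive protein may lie downstream of the outcome. Creatinine is also on the list; its link to muscle is general physiology and is not stated in the article.
- Calories and protein come from the same diet and enter together.

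At stake is the reading of the intake result. A null coefficient could reflect no association, adjustment for a consequence of muscle change, or collinearity. A positive one could reflect severity. The written model would not tell these apart.

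**Working it through.** The article gives no figure to reproduce: no sample size, effect size, correlation or laboratory timing. The check is therefore a comparison of the text, followed by illustrations in which every numerical input is assumed.

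**Text.** Section 2.2 names seven laboratory items. With calories and protein, the model has at least 7 + 2 = 9 predictors if each item enters once. None is admission thickness or a severity score. The outcome is loss in section 2.2 and in the first half of the section 3.4 sentence, but muscle mass in the second half.

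**Severity left out.** Take standardised variables: intake X = -0.5S + noise, outcome Y = 0.3X - 0.4S + noise, where S is severity.

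- Without S, the intake coefficient is 0.3 + (-0.4)(-0.5) = 0.50, against a true 0.30.
- With a laboratory proxy for S, correlated ρ with it, the coefficient is 0.3 + 0.2(1 - ρ²)/(1 - 0.25ρ²).
- For ρ = 0.3, 0.6 and 0.9 this gives 0.49, 0.44 and 0.35. Simulation gave the same values.

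So omitting severity can overstate the association, and a laboratory value that only marks severity corrects part of that.

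**Laboratory value downstream of muscle.** Take Y = bX + e with b = 0.3, so var(e) = 1 - 0.09 = 0.91, and C = gY + u with var(u) = 1 - g². Given C, the intake coefficient is b × var(u)/(var(u) + g² var(e)). At g = 0.5 the fraction kept is 0.75/(0.75 + 0.25 × 0.91) = 0.75/0.9775 = 0.77.

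| Correlation of C with outcome | Share of intake coefficient kept |
|---|---|
| 0.1 | 99% |
| 0.3 | 92% |
| 0.5 | 77% |
| 0.7 | 53% |

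**Laboratory value taken at admission.** Suppose creatinine reflects only admission muscle (correlation 0.3 or 0.5), intake is unrelated to admission muscle, and the change has an SD of about 0.4 of the admission SD. The simulated intake coefficient is 0.119 without and 0.119 with creatinine for the level, and 0.121 and 0.121 for the change. There is no attenuation. Level and change also give essentially the same coefficient here, so in this setting the choice of outcome matters for precision. It would matter for bias if intake were related to admission thickness.

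**Calories and protein together.** The standard error is multiplied by sqrt(1/(1 - r²)), where r is their correlation. At r = 0.9 this is sqrt(1/0.19) = 2.29.

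| Assumed r | 0.5 | 0.7 | 0.8 | 0.9 | 0.95 | 0.98 |
|---|---|---|---|---|---|---|
| SE multiplier | 1.15 | 1.40 | 1.67 | 2.29 | 3.20 | 5.03 |

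This widens intervals; it does not bias the coefficients.

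**The case against.** The strongest reply is that section 2.2 treats laboratory changes as exposures of equal standing with intake in a descriptive analysis. The article never calls them an adjustment set, and never claims a causal intake effect. Which values enter, and when they are taken, are details that a condensed article may leave to the full plan. If the laboratory values mark severity, including them may reduce bias. Fitting calories and protein separately would let each coefficient absorb the other.

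Much of this stands. A reader might infer that the intake coefficients will be attenuated. The documents do not support that: attenuation needs laboratory values downstream of muscle, their timing is not given, admission creatinine need not change the coefficient, and a severity proxy can move it towards the truth. A reader might also infer from nine or more predictors that the model is overfitted. That needs the number of patients, which the article does not give, and its absence from a condensed article is no fault. Strong collinearity is plausible but not documented, and whether to enter both nutrients together is a trade-off.

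What the reply does not meet is what the article does state. The named outcome differs from the stated aim, and severity, which the authors say can affect thickness, is missing from the named predictors. The only model described mixes intake with variables that, on the article's own background, may follow from muscle change. Even as a description, its intake coefficient is conditional on those values and is not the plain association with loss.

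**Conclusion.** The point holds as a weakness in how the secondary analysis is specified. The intake coefficients from the section 3.4 model can be confounded by severity, attenuated if post-admission laboratory values lie downstream of muscle, and imprecise if calories and protein are strongly correlated. The first two can pull in opposite directions, so neither the net direction nor the size can be stated; the figures above are illustrations only. The conclusion assumes the natural reading that intake and laboratory values share one model. The primary comparison of ultrasound with CT is not affected. The change is worth making because it is cheap, uses data already collected, and matches the stated interest in muscle loss.

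**What to change.** In section 3.4, make the main intake analysis a regression of change in quadriceps thickness (for example, first to third measurement) on intake. Adjust it for admission thickness and for one severity score already collected (injury severity score, SAPS-3 or APACHE II), chosen in advance. Leave post-admission laboratory values out of this model. Report the laboratory associations, creatinine included, in a separate model labelled exploratory. Keep the combined model only as a sensitivity analysis. State when each laboratory value is taken.

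The cost is some wording and a few more model runs, with no new measurements. The downside is that the main intake model does not adjust for renal function; the combined sensitivity model gives some view of that.

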### 3.5. Data management

Data will be collected directly from the USG and CT device and will be stored to ensure reliability.

All participants will receive a numerical identification of the study itself. Personal data will be stored in the hospital’s digital system, protected by a password to ensure confidentiality.

Any modifications or side effects to the protocol will be communicated to REBEC.gov and to the Research Ethics Committee and clinical research unit of Hospital das Clínicas da Faculdade de Medicina de Ribeirão Preto by the responsible researcher.

All principal investigators will have access to the final trial dataset.

## 4. Discussion

Skeletal muscle function depends not only on the quantity of muscle but on the quality, and this is also adversely affected in critically ill patients. Changes in muscle echogenicity that occur early in critically ill patients are related to necrosis and myofibrosis when evaluated in histological sections.^[29]^

In assessing strength, the medical research council sum score < 48/60 has been used, a subjective analysis tool that is not able to accurately assess. Muscle biopsy and neural conduction tests are more accurate measures, but they are more invasive and less feasible in clinical practice.^[10]^

Recent studies show that the echogenicity of muscle ultrasound is correlated with muscle architecture, fat infiltration, fibrosis, and muscle necrosis. Normal musculature is hypoechogenic (dark). An increase in echogenicity, a lighter or brighter appearance, may represent muscle necrosis or fatty infiltration.^[10]^ The early identification of these patients is important, because they are predictors of functionality, morbidity and mortality, and their early identification can change their clinical outcome.^[10]^

Although some studies,^[30,31]^ using USG have shown disappointing results, USG performed strictly none of them in critically ill patients on mechanical ventilation and used the sectional area as a method of measuring muscle loss. Evaluation of quadriceps muscle thickness by USG revealed over the first week of critical illness a 5% greater chance of mortality at 60 days.^[32]^

A published study,^[33]^ used ultrasound to recognize muscle wasting in patients with sepsis in the ICU, found a significant association between muscle loss, infection and organ dysfunction, besides patients who had greater muscle mass loss having more complications after ICU discharge and greater mortality rate. It was identified that the most significant losses of muscle mass occurred in the first days of hospitalization and preventive care in this muscle loss should be performed as soon as possible. Thus, the authors recommend the use of ultrasound as a tool to predict prognosis in patients with sepsis in the ICU.

Decreased muscle thickness in mechanically ventilated patients showed that quadriceps muscle layer thickness loss was associated with 60-days mortality.^[32]^

Another observational study,^[34]^ aimed to evaluate the role of muscle ultrasound in the analysis of nutritional status in 29 patients admitted to the ICU, identified the greatest loss of muscle mass in the first week of hospitalization, having a direct association with the patient’s nutritional status. Although BMI is a commonly used parameter for screening nutritional status, it does not show the amount of muscle loss in these patients.^[35,36]^ In contrast, USG is a valuable and practical measurement tool that may hold promise in helping to guide metabolic support that allows morphological changes in muscles to be assessed in critically ill patients.^[37]^

It is also important to note how safe and viable the tool is. In patients with severe trauma, the use of quadriceps USG was easy to perform and reliable even in the hands of less experienced operators.^[38]^ Thus, USG ends up gaining ground for its ease of use and lower costs.

Our study can contribute to the use of USG in critically ill patients with muscle loss, not only by recognizing patients with a more fragile nutritional component but also by differentiating the more severe patients who are at greater risk of unfavorable evolution in the ICU. We believe USG is a noninvasive and easy-to-operate tool to distinguish patients on mechanical ventilation who have muscle wasting by analyzing quadriceps thickness, and thus early approaches could be applied to optimize treatment.

The novelty and importance of this project lies in using a method for assessing muscle mass through ultrasound of the quadriceps femoris, a noninvasive, low-cost bedside method that is feasible in critically ill patients.

In this study, we propose, unprecedentedly, performing a validation study of ultrasound with the gold standard (GS) to evaluate the musculature of critically ill patients victims of traumatic brain injury. The results got will be fundamental for the development of new fields of investigation and may contribute to the discovery of a new approach to treat sarcopenia in critically ill patients.

This study has limitations, such as the characterization of the study population in terms of age and sex, trauma severity, fluid balance, and associated comorbidities, which can affect both muscle thickness and outcomes. In addition, this is an observational study in a single center, which certainly has limitations in the patient profile and regional variations.
